**Table 1 Tab1:**
[figure not shown]
Sample timetable with INTREPRET program components incorporated into therapeutic community-based treatment platform

CBT: cognitive behavioral therapy, PE: psycho-education, SHGM: self-help group meeting, SS: social support meeting. All these activities are treatment elements of INTREPRET

Patients in the control group receive TAU based on the TC approach. Typically, patients participate in a variety of daily activities designed by the TRCs, including therapeutic meetings, physical activities, education, religious gatherings, and house-keeping activities [18]. During the trial, the participants receive ancillary care, including medical care other than treatment for drug use and the opportunity to participate in religious services. Following discharge from the treatment program, all participants will receive aftercare services that include booster sessions and family therapy.

### Therapists

The therapists in both groups are psychologists or social workers. The psychologists who provide the INTREPRET sessions to the intervention group receive specifically developed 5-day training for this study, consisting of lectures and hands-on group sessions on (1) INTREPRET administration, (2) facilitation standards, (3) CBT, and (4) motivational interviewing, followed by 3-month dry run sessions. The trainers are experienced psychologists and psychiatrists who had participated in Matrix training in the USA in 2017 and 2018. Moreover, treatment integrity is monitored by trainers during the dry run period using a fidelity checklist developed before the trial [17]. The researchers monitor treatment implementation on a random basis to ensure the quality of treatment using a fidelity checklist.

### Data collection and research instruments

Outcome data are collected in three phases: pre-treatment, post-treatment, and 3-month follow-up (Table 2). To collect data on the primary outcome (i.e., drug use), urine testing for stimulants is to be implemented only during follow-up. In addition, self-administered questionnaires are used to collect outcome data on self-reported stimulant use and to determine patient demographic and psychosocial variables. To measure psychological variables, several psychometric scales are to be employed at baseline, pre-discharge, and follow-up, as follows:
A Drug Abuse Screening Test 20 (DAST 20) that screens drug-related disorders [19]The Addiction Severity Index-Self Report (ASI-SR) that evaluates the severity of drug-related problems [20]The Simulant Relapse Risk Scale (SRRS) that evaluates relapse risk of stimulant use [21]The Visual Analogue Scale (VAS) for craving that evaluates the subjective magnitude of drug craving [22]The Coping Behaviors Inventory-Drug (CBI-Drug) that evaluates coping behaviors related to drug use [23]The Brief Coping Orientation to Problems Experienced (Brief COPE) that evaluates the general coping repertoire [24]The World Health Organization Five Well-being Index (WHO-5 Well-being Index) that assesses overall well-being [25]The Five-Level EQ-5D (EQ-5D-5L) that evaluates health-related quality of life, including mobility, self-care, usual activities, pain/discomfort, and anxiety/depression [26]The Beck Depression Inventory II (BDI-II) that screens for depression [27]Perceptions of care surveys (PoC) that evaluate self-reported care satisfaction [28]

**Table 2 Tab2:** Assessment at different time points

	Time point		
Variables/scales	Pre-treatment	Post-treatment	3-month follow-up
Socio-demographics	X		
Drug use experience	X		
Urine test			X
Self-report drug use	X		X
DAST 20	X		X
ASI-SR	X		X
SRRS	X	X	X
VAS for craving	X	X	X
AUDIT	X		X
CBI-Drug	X		X
Brief COPE	X	X	X
WHO-5 Well-being Index	X	X	X
EQ-5D-5L	X	X	X
BDI-II	X	X	X
PoC		X	

*DAST* Drug Abuse Screening Test, *ASI-SR* Addiction Severity Index-Self Report, *SRRS* Stimulant Relapse Risk Scale, *VAS* Visual Analogue Scale, *AUDIT* Alcohol Use Disorder Identification Test, *CBI-Drug* Coping Behaviors Inventory-Drug, *COPE* Coping Orientation to Problems Experienced, *WHO-5 Well-being Index*, the World Health Organization Five Well-being Index, *EQ-5D-5L* Five-level EQ-5D, *BDI * Beck Depression Inventory, *PoC* Perceptions of Care Surveys

The DAST 20 and the SRRS were translated into Tagalog and back-translated into English. The original and back-translated versions were checked for discrepancies by three researchers including a native Tagalog speaker, and final versions were agreed. In terms of reliability, the DAST 20 had an *α* value of 0.81. Concerning validity, receiver-operating-characteristic analysis, featuring diagnoses from independent doctors, returned an acceptable area-under-curve value of 0.62. Acceptable reliability was also confirmed for the SRRS, with an *α* value of 0.89. The correlation analysis of subjective drug craving (measured using the VAS) and the SRRS revealed a significant positive correlation (*r* = 0.19, *p* < 0.001), indicating adequate validity.

To ensure the anonymity and privacy of the participants, all data are de-identified and managed using codes at the data entry and analysis stages. Data are to be anonymized in a linkable fashion, involving a separate table that links the participants’ codes and names, and carefully stored with access only by designated personnel. All data are collected by the trained data collection team, and researchers monitor the data collection activities on a random basis to ensure compliance with the protocol.

### Data analysis

The following two types of regression equations are estimated to calculate the causal effect of providing residential treatment on outcomes:
For the primary outcome indicator of urine testing, regression model (1) was estimated to test any statistically significant difference in means between the intervention and control groups:

1$$ {Y}_{ij}=\alpha +\beta {T}_i+\theta {X}_i+{v}_j+{\omega}_{ij} $$

where *Y*_*ij*_ is the urine test result of patient *i* at TRC *j*, *α* is a constant that gives the value of the urine test result for the control group, *T*_*i*_ is the treatment dummy, *X*_*i*_ is the set of patient characteristics to be controlled for, such as age and education, *v*_*j*_ is a TRC-level error term, and *ω*_*ij*_ is an individual error term.

This study estimates the coefficient of the treatment dummy (*β*), which shows the between-group difference. Since the urine test has a binary result, the log odds of the outcome are to be estimated as a linear combination of the independent variables using logistic regression (i.e., logit (*Y*_*ij*_)) rather than linear regression.
2)For the secondary outcome indicators of the psychometric tests, which are to be measured both at baseline and follow-up, regression model (2) with an interaction term is estimated to calculate a difference-in-difference (DD) estimate that relies on a comparison of the intervention and control groups before and after the intervention [29]:

2$$ {Y}_{ijt}=\alpha +\beta {T}_{i1}t+{\rho T}_{i1}+\gamma t+\theta {X}_i+{v}_{jt}+{\omega}_{ijt} $$

where *Y*_*ijt*_ is the psychometric test result of patient *i* at TRC *j* at time *t*, *α* is a constant giving the average value of the psychometric test result for the comparison group at time *t*_0_ (baseline), *T*_*i*1_ is the treatment dummy, *t* is the time dummy, *X*_*i*_ is the set of patient characteristics to be controlled for, *v*_*j*_ is a TRC-level error term, and *ω*_*ij*_ is an individual error term.

The study estimates the coefficient (*β*) on the interaction between the treatment dummy (*T*_*i*1_) and the time dummy (*t*), which gives the average DD effect of the intervention. In addition to this interaction term, the variables *T*_*i*1_ and *t* are included separately to identify any separate mean effects of time as well as the effect of being targeted versus not being targeted.

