### Sample size calculation

Based on recently published findings from a systematic review that included studies with a similar design [7], this study considered a minimum detectable effect of 0.23 and a population standard deviation of 0.42. With a significance level of 0.05, and a power of 0.95, a sample size of 88 participants per group (or 176 patients in total) was determined as needed to test the causal effect of the intervention.

Based on preparatory field study experience, it is possible that more than half of the participants may drop out of the study by not showing up for the follow-up interviews in the three months after discharge. Given a coverage rate of 44%, the final required sample size needed to be adjusted to 200 patients per group (or 400 patients in total) to achieve a sample size of 88 patients per group (or 176 patients in total).

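### Model (2) does not link a patient's baseline and follow-up scores: power is lost on the psychometric outcomes, and bias follows if loss depends on baseline differently in the two arms

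*Protocol article*

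**What the plan says.** For the psychometric outcomes, "which are to be measured both at baseline and follow-up", the Data analysis section of the protocol article states that "regression model (2) with an interaction term is estimated to calculate a difference-in-difference (DD) estimate". It prints model (2) in full: a constant α, treatment × time (β), treatment (ρ), time (γ), patient characteristics X_i (θ), a TRC-level error v_jt and a residual ω_ijt. The target is β, "which gives the average DD effect of the intervention". The treatment and time terms "are included separately to identify any separate mean effects of time as well as the effect of being targeted versus not being targeted".

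The legend under the equation writes the two errors as v_j and ω_ij, without the time index that the equation gives them, and says of ω_ij that it "is an individual error term". The section does not say whether errors are independent over time or how standard errors are computed. The Sample size calculation section expects 44% coverage at follow-up, that is 88 of 200 patients per arm.

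**The concern.** Each patient contributes a baseline and a follow-up score, and these will be correlated. Nothing in the equation carries that correlation: there is no patient effect, no within-patient covariance, and the baseline score is an outcome row, not a covariate.

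Two things are at stake. First, if the errors are taken as independent, the standard error of β is not the standard error of a within-patient contrast. Second, if every available score is used, β compares the baseline of all randomised patients with the follow-up of the minority who attend, and the model has no means of correcting for a change in who is observed. The model also estimates a baseline difference between arms that randomisation makes zero in expectation, which costs precision. Psychosocial well-being is part of the trial's stated aim, so these analyses matter although they are secondary.

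**Working it through.** **Inputs from the article.** "a minimum detectable effect of 0.23 and a population standard deviation of 0.42"; "With a significance level of 0.05, and a power of 0.95"; 88 followed up and 200 randomised per arm; 44% coverage; 1:1 allocation.

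**Assumptions, not in the documents.** Within-patient correlation r of 0.3, 0.5 and 0.7 (what remains after X_i); equal variance at both times, scaled to SD 1; a 0.4 SD effect for power; the retention slopes given below. TRC terms are neglected.

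**Step 1: the plan's own figures.** Two-sided, 2 × (1.960 + 1.645)² × 0.42² / 0.23² = 86.7, so 87. The exact noncentral-t calculation needs 88 (power 0.951). 88 / 0.44 = 200. Both stated sizes reproduce.

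**Step 2: standard error of β, loss unrelated to the scores.**

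- All available scores, independent errors: √[2(1/88 + 1/200)] = 0.181.
- All available scores, true: √[2(1/88 + 1/200 − 2r/200)]. At r = 0.5 this is √(2 × 0.01136) = 0.151.
- Complete pairs, independent errors: √(4/88) = 0.213. True: √[4(1 − r)/88]. The ratio is 1/√(1 − r).

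| r | All scores: printed / true SE | Ratio | Actual type I error | Pairs: printed / true SE | Ratio | Actual type I error |
|---|---|---|---|---|---|---|
| 0.3 | 0.181 / 0.164 | 1.11 | 0.030 | 0.213 / 0.178 | 1.20 | 0.019 |
| 0.5 | 0.181 / 0.151 | 1.20 | 0.019 | 0.213 / 0.151 | 1.41 | 0.006 |
| 0.7 | 0.181 / 0.137 | 1.32 | 0.010 | 0.213 / 0.117 | 1.83 | 0.0003 |

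Actual type I error is 2[1 − Φ(1.96 × ratio)], against a nominal 0.05.

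**Step 3: power for 0.4 SD.** With the printed SE on all scores at r = 0.5, the estimate must exceed 1.96 × 0.181 = 0.355, so power is Φ[(0.4 − 0.355)/0.151] = 0.62. With the correct SE it is Φ(0.4/0.151 − 1.96) = 0.76. A likelihood model linking the scores has SE √{2[(1 − r²)/88 + (1 − r)²/200]} = 0.140. ANCOVA has SE √[2(1 − r²)/88] = 0.131.

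| r | As printed, all scores | Same estimate, correct SE | Linked likelihood model | ANCOVA |
|---|---|---|---|---|
| 0.3 | 0.609 | 0.687 | 0.706 | 0.794 |
| 0.5 | 0.618 | 0.756 | 0.816 | 0.865 |
| 0.7 | 0.630 | 0.832 | 0.947 | 0.960 |

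**Step 4: selective loss.** Simulation with 4,000 runs per setting, 200 randomised per arm, 44% retained on average, no true effect. Bias in SD units:

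| Retention depends on | r | Model (2), all scores | Paired change | Linked likelihood | ANCOVA |
|---|---|---|---|---|---|
| Baseline, same slope in both arms (−0.7 log-odds per SD) | 0.3 to 0.7 | 0.00 | 0.00 | 0.00 | 0.00 |
| Baseline, intervention arm only (−0.7) | 0.3 | −0.10 | +0.25 | 0.00 | 0.00 |
| As above | 0.5 | −0.18 | +0.17 | 0.00 | 0.00 |
| As above | 0.7 | −0.25 | +0.11 | 0.00 | 0.00 |
| Follow-up score, intervention arm only (−0.7) | 0.5 | −0.35 | −0.17 | −0.26 | −0.27 |

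In the one-arm baseline setting, model (2) with its printed SE rejects a true null in 6.5%, 12% and 22% of runs.

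A hand check: let δ be the shift in mean baseline among attenders in the affected arm. Model (2) on all scores is then biased by rδ and paired change by −(1 − r)δ, so the first minus the second equals δ. At r = 0.5 this gives −0.180 − 0.173 = −0.353. Then rδ is −0.106, −0.177 and −0.247, in line with the simulation. If δ is the same in both arms, it cancels.

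**The case against.** The strongest reply is that the equation gives a mean model and names its errors. It does not declare ω_ijt independent over time, and patient-clustered standard errors would repair the SE without touching the equation. Variance estimation is something an article may leave to the full protocol or analysis plan. This stands, so the SE statement has to be conditional. It does not dispose of the point: the model is printed in full without the patient, and clustering would neither recover the precision of baseline adjustment nor remove the bias in Step 4.

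A second reply is that the legend's ω_ij, lacking a time index, is a patient effect. This does not stand. Model (1) uses the same symbol and description for an ordinary residual, and if ω_ij were a patient effect no residual over time would remain in model (2).

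A reader might also infer more than the documents support:

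- That the SE error produces false positives. For positive r it does the reverse.
- That any selective loss distorts β. The bias needs baseline dependence that differs between arms, and the article gives a single coverage figure with no evidence of differential loss.
- That the 41% SE excess and the selection bias occur together. The first belongs to 88 complete pairs, the second to 200 baseline and 88 follow-up scores, where the excess at r = 0.5 is 20%.
- That every psychosocial outcome is affected. Perceptions of care is collected only post-treatment (Table 2), so model (2) cannot apply to it.

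**Conclusion.** The point holds as a specification weakness in the analysis of the psychometric outcomes measured at baseline and follow-up. Fitted as printed with independent errors, the test is conservative. The SE excess is 11% to 32% on all scores or 20% to 83% on complete pairs for r from 0.3 to 0.7, and at r = 0.5 all-score power for 0.4 SD is about 62% where 76% to 86% is attainable. The risk of bias, about −0.1 to −0.25 SD in the scenario examined, is conditional on loss that depends on baseline differently by arm. That is plausible when more than half may be lost and the arms differ in programme and dormitory, but it is not shown. The correlation, effect size and retention slopes are assumptions.

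The primary urine result is analysed by model (1), with one measurement per patient, and is untouched. This should be fixed, but it does not threaten the trial's main conclusion.

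**What to change.** Replace model (2) with one of these:

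- ANCOVA of the follow-up score on arm, baseline score and TRC, with the planned covariates; or
- a likelihood-based mixed model with unstructured within-patient covariance and the arms' baseline means constrained equal. Under the assumptions above, this has the same precision for the treatment effect as ANCOVA.

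Reconcile ω_ij with ω_ijt and v_j with v_jt, and state the missing-data assumption on which the analysis rests. Neither option removes bias if loss depends on the unseen follow-up score in one arm only, so that limit should be acknowledged.

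Two lighter repairs are not adequate. Patient-clustered standard errors correct only the SE. A patient fixed effect, or paired change on completers, is still biased under one-arm baseline-dependent loss, and at r = 0.3 by more than model (2) itself (+0.25 against −0.10 SD).

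The cost is a revised model statement and analysis code, with no new data or visits.

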### Patient and public involvement

Psychometric tools for outcome measurement have been pretested on approximately 40 patients in two TRCs and feedback comments obtained from the patients and staff members who observed the pre-test sessions. The treatment programs were implemented prior to the commencement of the study at all sites and feedback obtained from the patients and used to develop the tools and programs and to administer the study.

### Ethics and dissemination

This study does not anticipate that the participants will suffer any adverse effects, either physically or mentally. To our knowledge, previous studies with similar interventions have not reported any serious adverse effects. In cases of any significant negative events, the intervention would cease or be modified.

The following measures are implemented to ensure appropriate ethical standards:
Potential participants are given a summary of the study and a consent form. The consent form must be signed and dated by the participants prior to participation.The participants are duly informed that they can withdraw from the study at any time without any negative consequences.Participants are compensated for inconvenience and expenses when they attend the follow-up interview. Participants showing up and cooperating in the follow-up receive an honorarium of 500 pesos, whereas those responding to an interview by telephone receive 200 pesos.All patient data are treated as confidential data. Any personally identifiable information is removed from the datasets in a linkable anonymizing manner. Each participant has a unique study identification number, linked to their personal information, and the list for linkable anonymizing is kept in a locked cabinet in the project office.The consent forms and the questionnaire forms will be kept in a lockable cabinet at a Department of Health office for 5 years after all data collection is collected, and then shredded and disposed of.This study has been approved by the Single Joint Research Ethics Board of the Department of Health, Republic of the Philippines (SJREB-2019-27) and the University of Tsukuba Faculty of Human Sciences Ethics Committee, Japan (T2019-70).No researchers have any competing interests concerning the current study.

The results of the study are intended for dissemination to a wide range of audiences through presentations and publication. The results will be reported on clinicaltrials.org.

Any modifications to the protocol that may affect the conduct of the study, potential benefits to the patient, or patient safety, including changes in study objectives, study design, patient population, sample sizes, study procedures, or significant administrative aspects, requires a formal amendment to the protocol. Any such amendment must be agreed by the RWG and approved by the relevant research ethics board and committee prior to implementation.

## Discussion

This is the first randomized controlled trial to compare the residential CBT program and the TC model for methamphetamine users in the Philippines. The study aims to fill the gaps in the current knowledge and capacity by introducing a CBT-based treatment program to improve the psychosocial well-being of drug users in the Philippines.

Based on scientific evidence, many drug users in the Philippines do not have access to effective treatment, and consequently, their health and psychosocial well-being are threatened. Furthermore, for society as a whole, the drug problem presents challenges to all members' safety and well-being. The drug problem cannot be solved by punishment or violence. The United Nations suggested that it is important to provide appropriate support to drug users while promoting the protection of and respect for human rights and the dignity of all individuals in the context of drug programs, strategies, and policies [29].

If this study can introduce an effective treatment to the Philippines, thereby improving the drug users’ health and well-being, it can help improve the health, safety, and well-being of individuals, families, communities, and society. It is also expected that policymakers will recognize the benefits of the treatment and support drug users' rehabilitation and social reintegration, rather than promoting punishment and exclusion.

## Data Availability

The datasets generated and/or analyzed during the current study are available from the Harvard Database repository, https://dataverse.harvard.edu/dataset.xhtml?persistentId=doi:10.7910/DVN/CPRRYA Registration number: 10.7910/DVN/CPRRYA registered on 9 January 2021.

## Abbreviations

INTREPRET: Intensive Treatment and Rehabilitation Program for Residential Treatment and Rehabilitation Centers
JICA: Japan International Cooperation Agency
CBT: Cognitive-behavioral therapy
TC: Therapeutic community
